## Abstract

**Background:**

The consumption of brown rice, which contains bran and germ and is rich in fiber, micronutrients, and phytochemicals, can contribute to good physical, cognitive, and mental health. However, these health benefits and the relevant mechanisms have not been fully elucidated, especially in human subjects. Therefore, we will conduct a randomized controlled trial to examine the effects of a brown rice-derived supplement on various aspects of health and to elucidate the underlying mechanisms.

**Methods:**

This study will be a prospective, longitudinal, double-blind, randomized, placebo-controlled trial. Eighty healthy adults aged 20 to 64 years will receive 3.5 g/day of a brown rice-derived supplement or placebo for 12 weeks. We will assess immune-related and metabolic markers using transcriptome and metabolome analyses of blood samples, respectively, and evaluate the gut microbiota composition using stool samples, including 16S rRNA-based analysis, with short-chain fatty acids also measured. Cognitive function, constipation, sleep, mood state, and health-related quality of life will also be assessed using validated assessments at baseline and at the endpoint. Between-group comparisons will be conducted using appropriate statistical methods according to the distribution and characteristics of the data.

**Discussion:**

This study is the first to examine the effects of a brown rice-derived supplement on various aspects of health, including immune, cognitive, physical and mental health. We hypothesize that changes in the variation in the gut microbiota play a key role in the mechanisms underlying these health effects; therefore, we will investigate how changes in the gut microbiota caused by the consumption of the brown rice-derived supplement affect health status. We hope that the information derived from this study will be useful for promoting the use of brown rice-derived supplements as a healthy food and improving public health.

**Trial registration:**

University Hospital Medical Information Network Clinical Trials Registry (UMIN-CTR), UMIN000049330. Registered on 8 November 2022. https://rctportal.niph.go.jp/en/detail?trial_id=UMIN000049330

## Introduction

### Background and rationale {6a}

Considerable attention has been given to the consumption of whole grains to improve health conditions. In the case of rice, accumulating evidence has suggested that the consumption of brown rice, which contains bran and germ and is rich in fiber, micronutrients, and phytochemicals [1, 2], can improve physical health (e.g., immune function, sleep, and obesity control) [3–7], cognitive health (e.g., general cognitive function and executive function), and mental health (e.g., depression and anxiety) [2, 8–10]. However, these health benefits have not been fully elucidated, especially in human subjects. For example, the positive effects of γ-oryzanol—a mixture of lipids that are abundant in brown rice—on the immune system have been demonstrated in animals through in vivo and in vitro studies but not in humans [11, 12]. Moreover, the mechanism underlying the health benefits of brown rice consumption remains unclear. Therefore, it is important to clarify the health benefits of brown rice and the mechanism underlying these beneficial effects to promote the consumption of brown rice from a public health perspective.

Regarding the mechanism underlying the beneficial effects of brown rice consumption, we assume that one of the important factors associated with these positive effects on health may be the change in intestinal microbial ecology caused by the consumption of brown rice. Whole grains balance the gut microbial ecology by increasing microbial diversity and inducing compositional alterations that benefit the host [3, 4]. Recent studies have reported that consuming brown rice positively affects the intestinal environment and improves physical health. A human study reported that consumption of a beverage made from brown rice for 4 weeks led to increases in the abundance of beneficial species in the intestine, which were associated with reduced inflammation and increased short-chain fatty acid production in patients with metabolic syndrome [13]. These results indicate that the consumption of brown rice exerts a positive effect on the immune system by changing the composition of the gut microbiota. The reason for this effect may be that brown rice is rich in dietary fiber, which produces short-chain fatty acids in the intestines, thereby positively affecting the immune system. Another study reported that consuming brown rice decreases the serum levels of inflammatory factors such as IL-6 and IL-8 by balancing peripheral blood mononuclear cells (PBMCs) and increasing short-chain fatty acids (SCFAs) in the gut [14]. However, this study did not capture the whole effect on the immune system because it specifically examined cytokines. Furthermore, the abovementioned studies were limited to individuals with metabolic symptoms and thus did not report how brown rice functions in the immune system in the general adult population, including individuals without health problems. Previous studies have suggested that certain dietary habits have a positive effect on the immune system and maintain a good health status in healthy adults [15–17]. Additionally, knowledge regarding the various health-related effects of brown rice, as well as knowledge of the immune system, has been very limited in humans. For example, brown rice may modulate the gut microbiota and thus affect physical and cognitive health [18–21]. Regarding obesity, animal studies have suggested that the intestinal microbiota affects obesity by prompting reward signals in the dopaminergic system [22, 23]. However, these mechanisms have not been elucidated in humans. Additionally, a healthy gut environment that balances microbiota diversity contributes to good mental health, but no previous study has investigated how brown rice consumption can balance the gut microbiome environment and how this phenomenon affects mental health [24].

Furthermore, despite its overall health benefits, brown rice is not widely accepted for consumption in daily meals. One of the problems with the frequent intake of brown rice is its hard texture even after cooking [25, 26]. This hard texture occurs because the wax in the outermost layer of brown rice grains inhibits water absorption [27]. To address this issue, we focus on the use of a brown rice-derived supplement as an alternative to eating brown rice. The brown rice-derived supplement that we will use in the present study includes the key nutrient-rich parts of brown rice, extracted and made into powder, thus making it easy to consume the active ingredients contained in brown rice for health purposes. Among these constituents is γ-oryzanol, which is a characteristic component of brown rice and has been suggested to exert beneficial effects on metabolic and inflammatory processes in experimental studies [11, 12, 18]. In addition, dietary fiber may be relevant to the present trial because it can influence the gut microbiota and related immune regulation [13, 14]. Therefore, this supplement may influence health through multiple biological pathways, especially immune function and gut microbiota-associated mechanisms. However, the effects of brown rice-derived supplements on physical, cognitive, and mental health have not been examined. When the health-promoting efficacy of food products is being examined, distinct products need to be examined separately if they have substantially different amounts and ratios of components, even if they are derived from the same food; there are likely synergistic interactions between components, and differences in composition can strengthen or weaken the effects of consuming specific products [28, 29].

### Objectives {7}

The objective of this trial is to perform a longitudinal investigation of the influence of consuming a brown rice-derived supplement for 12 weeks on multiple health-related outcomes in healthy adults. In particular, we will assess measures related to immune function, gut microbiota, cognitive function, mental and physical health, sleep, constipation, and health-related quality of life (HRQOL). We hypothesize that participants receiving the brown rice-derived supplement will show favorable changes in these outcomes compared with those receiving placebo and that changes in the gut microbiota may partly underlie these effects. Therefore, we will also examine the relationships between changes in the gut microbiota and various health aspects derived from the consumption of the brown rice-derived supplement.

### Trial design {8}

This study will be a longitudinal, double-blind, randomized, placebo-controlled prospective intervention trial with a parallel group of healthy adults (see Fig. 1 for an overview of the planned trial design). We designed this study to explore the effects of brown rice-derived supplementation on various health outcomes, including the immune system, cognitive function, gut microbiota, constipation, sleep, and HRQOL. Participants will be randomly assigned to the brown rice-derived supplement group or the placebo group at a ratio of 1:1. This protocol is in accordance with the Standard Protocol Items: Recommendations for Interventional Trials checklist [30]. This study protocol was approved by the Ethics Committee of Tohoku University Graduate School of Medicine (IRB# 2022–1–845) and preregistered in a clinical trial registry (UMIN-CTR ID: UMIN000049330). The committee has peer-reviewed the progress of the study, independent of our research team.

**Fig. 1 Fig1:**
[figure not shown]
Overview of the planned trial design

## Methods: participants, interventions and outcomes

### Study setting {9}

The study will be conducted at the Smart-Aging Research Center of Tohoku University (Japan), and all the data will be collected at the center.

### Eligibility criteria {10}

The inclusion and exclusion criteria for participation in this trial are listed in Table 1.

**Table 1 Tab1:** Inclusion and exclusion criteria

Inclusion criteria	Exclusion criteria
• Adults aged 20 to 64 years at registration • Having a willingness to consume experimental products daily for 12 weeks at the entry • Informed consent can be obtained	• Estimated IQ < 80 • Severe visual and hearing impairment • Having habits of consuming brown rice and related supplements in the past year • Pregnancy or breastfeeding • Currently participating in other clinical trials • Following disease with a severe level – Endocrine and metabolism disease – Heart disease – Digestive system disease – Severe allergic disease – Dementia and neurological disease – Psychiatric disorder • Other reasons for difficulties in carrying out the research

### Who will take informed consent? {26a}

The research staff will obtain informed consent from potential participants who have been deemed preliminarily eligible. After the staff has determined eligibility and thoroughly explained the details of the study, potential participants will have the opportunity to ask questions. If participants are willing to participate in the study, they will sign the informed consent document.

## Interventions

### Explanation for the choice of comparators {6b}

We will use maltodextrin colored with edible food dye to resemble the brown rice-derived supplement used in this study. The reason for the use of maltodextrin is that it is similar in texture and taste to the brown rice-derived supplement.

### Intervention description {11a}

The participants who are assigned to the brown rice-derived supplement group will receive 3.5 g of the brown rice-derive supplement per day orally (“Kinme Mai Ekisu” from Toyo Rice Corp., Wakayama, Japan) for 12 weeks. The brown rice-derived supplement includes nutrient-rich parts of brown rice that have been extracted and made into powder. It contains several bioactive components that may be relevant to the present trial, particularly γ-oryzanol and dietary fiber. The participants who are assigned to the placebo group will receive 3.5 g of placebo per day orally. The placebo will have a similar appearance to the brown rice-derived supplement. The supplement and placebo will each be packaged in a 3.5 g stick, and participants will be instructed to consume one stick per day at any time of day they choose. Both the supplement and placebo will include only products that have been confirmed to be safe in Japan and have been marketed as food products. The supplement and placebo are not expected to cause serious adverse effects. The nutritional information of the brown rice-based supplement and placebo is shown in Table 2.

**Table 2 Tab2:** Nutrient composition of brown rice-derived supplement and placebo

	Brown rice-derived supplement		Placebo	
	Per 100 g	Per package (3.5 g)	Per 100 g	Per package (3.5 g)
Protein	17.3 g	0.61 g	< 0.1 g	< 0.01 g
Crude fat	26.4 g	0.92 g	< 0.1 g	< 0.01 g
Carbohydrates	40.3 g	1.41 g	95.3 g	3.34 g
Sugar	23.0 g	0.81 g	94.3 g	3.30 g
Dietary Fiber	17.3 g	0.61 g	1.0 g	0.04 g
Calories	433.0 kcal	15.16 kcal	379.0 kcal	13.27 kcal
Sodium	14.1 mg	0.49 mg	86.4 mg	3.02 mg
Phosphorus	2710.0 mg	94.85 mg	1.1 mg	0.04 mg
Iron	9.83 mg	0.34 mg	N/A	N/A
Calcium	58.1 mg	2.03 mg	N/A	N/A
Potassium	2020.0 mg	70.70 mg	N/A	N/A
Magnesium	1130.0 mg	39.55 mg	0.2 mg	0.01 mg
Copper	0.7 mg	0.02 mg	N/A	N/A
Zinc	8.8 mg	0.31 mg	N/A	N/A
Manganese	15.4 mg	0.54 mg	N/A	N/A
Thiamine	4.6 mg	0.16 mg	N/A	N/A
Vitamin B6	3.6 mg	0.13 mg	N/A	N/A
Folic acid	97.0 μg	3.40 μg	N/A	N/A
Niacin	47.4 mg	1.66 mg	N/A	N/A
α-Tocopherol	19.5 mg	0.68 mg	N/A	N/A
β-Tocopherol	0.8 mg	0.03 mg	N/A	N/A
γ-Tocopherol	2.3 mg	0.08 mg	N/A	N/A
δ-Tocopherol	0.1 mg	0.004 mg	N/A	N/A
GABA	214.0 mg	7.49 mg	N/A	N/A
Ferulic acid	0.3 g	0.01 g	N/A	N/A
γ-oryzanol	200.0 mg	7.00 mg	N/A	N/A
Lipopolysaccharide	3440.0 μg	120.40 μg	0.6 μg	0.02 μg

*GABA* Gamma-aminobutyric acid, *N/A* Not available

### Criteria for discontinuing or modifying allocated interventions {11b}

We do not expect serious adverse effects to occur after consumption of the brown rice-based supplement or the placebo. However, if a participant wishes to discontinue the consumption of experimental products due to poor physical condition experienced during the intervention period, the intervention will be stopped for that individual. In the event of an allergic reaction to the experimental products, the intervention will be stopped immediately for the affected individual. The decision to discontinue consumption will be left to the individual participants, and any participant who chooses to discontinue the intervention will be asked to explain the reason. In this study, no modifications will be made regarding the allocated interventions or the dose of the experimental products.

### Strategies to improve adherence to interventions {11c}

During the intervention period, participants will complete a checklist that asks about the timing of consumption (morning, noon, or night) every day. In addition to the checklist, we will ask participants to fill out a web report system that was developed using Google Forms (Google LLC, CA, US) to report when they consumed the experimental product. The web report system will enable us to sequentially determine whether each participant has consumed the experimental product and to send reminders to participants if they have not consumed the stick by a certain time of day (ex. 19:00).

### Relevant concomitant care permitted or prohibited during the trial {11d}

We will ask participants to not intentionally change their eating habits. Participants will be allowed to take other supplements or medications, but they will be asked to report any new supplements or medications they take during the intervention period. In addition, we will ask participants to report their medical history, if any, during the intervention period.

### Provisions for posttrial care {30}

Severe adverse events, including unexpected allergic reactions resulting from the consumption of the brown rice-derived supplement or placebo, will be covered by clinical research insurance if the adverse effects result from the consumption of the supplement or placebo. Other potential physical harm will be covered by public insurance. There will be no posttrial care.

### Outcomes {12}

Previous studies have suggested that brown rice has various effects on human health, and we will present evidence concerning these effects and the underlying mechanisms by using a brown rice-derived supplement in this study. Therefore, the overall condition of the immune system, metabolism, constipation, sleep, cognitive function, mental health, and gut microbiota community composition will be co-primary outcomes for comprehensively examining various health aspects. Blood samples will be collected to analyze immune function and metabolism via transcriptome and metabolome analysis, respectively, and stool samples will be collected to evaluate diversity in the gut microbiota.

In addition, we will collect information on the factors that may influence the relationships between consumption of the brown rice-derived supplement and primary outcomes. Various lifestyles could influence the relationships between the consumption of the brown rice-derived supplement and broad health conditions. In particular, daily eating habits and physical activity may strongly impact these relationships. Therefore, we use the brief-type self-administered diet history questionnaire (BDHQ) and a simple questionnaire to evaluate total and domain-specific physical activity [31, 32]. In addition, we will collect data on the overall intelligence quotient (IQ) to control for the influence of IQ on the performance of cognitive tests [33].

Since this study aims to determine the effects of brown rice-derived supplement consumption on various health aspects, all sample collection and measurements, except for daily health, will be performed at two time points (baseline and endpoint), and we will compare the changes in these variables between and within groups. Daily health during the intervention period will be compared between groups. We assume that these variables will change in a positive direction if the brown rice-derived supplement is effective at improving human health.

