#### Daily health checks

We will ask participants to report their health status and body temperature on a daily check sheet. Specifically, participants will be asked to report the presence or absence of the following symptoms: sore throat, running nose, cough, phlegm, stomachache, diarrhea, loss of appetite, and lethargy/fatigue.

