### Adverse event reporting and harms {22}

Participants will be asked to actively report any adverse events that occur during the intervention period. The severity of any adverse events, irrespective of their relationship to the study intervention, will be documented in a case report form and assessed using the National Cancer Institute Common Terminology Criteria for Adverse Events v4.0.

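### The daily symptom sheet is not named as an adverse-event source, so gut symptoms ticked by participants who continue may be absent from the graded harms comparison

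*Protocol article*

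**What the plan says.** The protocol article treats daily symptoms in three places.

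- **Daily health checks (under {18a}).** "We will ask participants to report their health status and body temperature on a daily check sheet". The items, each recorded as present or absent, are "sore throat, running nose, cough, phlegm, stomachache, diarrhea, loss of appetite, and lethargy/fatigue". No total or composite score is stated.
- **Outcomes {12}.** Daily health is set apart from every other measure: "all sample collection and measurements, except for daily health, will be performed at two time points (baseline and endpoint"). For daily health the stated analysis is "Daily health during the intervention period will be compared between groups". The next sentence reads: "We assume that these variables will change in a positive direction if the brown rice-derived supplement is effective at improving human health". Daily health is not among the co-primary outcomes.
- **Adverse event reporting and harms {22}.** "Participants will be asked to actively report any adverse events that occur during the intervention period". Then: "The severity of any adverse events, irrespective of their relationship to the study intervention, will be documented in a case report form", with grading by CTCAE v4.0. The daily check sheet is not mentioned.

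Two other sections bear on the point. Table 1 excludes digestive and allergic disease only under the line "Following disease with a severe level", so milder long-standing complaints are compatible with entry. Section {11b} asks participants who stop the product for their reason.

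**The concern.** The trial will hold a day-by-day, blinded record of the complaints that would show whether an ingested powder is poorly tolerated. The text gives that record no role in the harms assessment. Grading depends on the participant deciding that a symptom is an adverse event and reporting it a second time. Many people will not do that for loose stools or a poor appetite that they have already ticked on a form.

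Outcomes {12} also speaks of one direction only, improvement, and makes no exception for the gut items, where a difference between arms could as well be a harm. The arms do differ in what reaches the gut: Table 2 gives 0.61 g of fibre and 0.92 g of fat per stick of supplement, against 0.04 g and less than 0.01 g for placebo.

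At stake is a harms table that understates mild gut symptoms, for a product that the authors hope to promote to healthy people. A smaller matter is that a comparison with no pre-treatment record cannot measure change and cannot adjust for symptoms that people already had.

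**Working it through.** The protocol gives no figure for this comparison, so there is nothing to reproduce. The check is first a reading of the text and then an illustration with assumed inputs.

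**1. Stated routes from a gut symptom to a graded adverse event**

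| Situation | Stated route |
|---|---|
| Participant reports it as an adverse event | Case report form and CTCAE grade ({22}) |
| Participant stops the product | Reason is asked ({11b}) |
| Participant starts a new medicine or supplement | New product is reported ({11d}) |
| Participant ticks it daily, continues, and does none of the above | None stated |

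The last row is the gap. Twelve weeks is 12 × 7 = 84 days. With three gut or appetite items that is 84 × 3 = 252 yes/no entries per participant, with no stated path to the case report form.

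**2. What the missing baseline costs**

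Inputs: 40 per arm (Sample size {14}), two-sided 5% and 80% power (assumed), and correlation r between pre-treatment and on-treatment symptom days (assumed).

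Detectable difference = (1.960 + 0.842) × √(2/40) × √(1 − r²) = 0.626 × √(1 − r²), in SD units.

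| r | Detectable difference | Power if the true difference is 0.5 SD |
|---|---|---|
| 0 (no baseline) | 0.63 | 61% |
| 0.3 | 0.60 | 65% |
| 0.5 | 0.54 | 73% |
| 0.7 | 0.45 | 88% |

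**3. How far long-standing symptoms could matter**

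Suppose, purely for illustration, that 10% of people have chronic symptoms on a share p of days, and the rest have symptoms on 5% of days with an SD of 6 points. For a pooled count, chronic status explains V/(V + 0.06²) of the between-person variance, with V = 0.10 × 0.90 × (p − 0.05)².

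- p = 80%: 0.0506/(0.0506 + 0.0036) = 93%
- p = 30%: 0.0056/(0.0056 + 0.0036) = 61%
- p = 20%: 0.0020/(0.0020 + 0.0036) = 36%

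The answer is set almost wholly by an assumption that the documents do not inform.

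**4. Simulation** (3,000 runs, 40 per arm, 84 days, all rates assumed). Placebo participants have on average one 5-day acute episode, and the supplement halves the number of episodes. Chronic participants have symptoms on half of days on average.

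| Chronic share | All symptom days pooled, no baseline | Pooled, 14-day run-in as covariate | Acute days only |
|---|---|---|---|
| 0% | 72% | 72% | 72% |
| 10% | 13% | 20% | 72% |
| 30% | 8% | 14% | 72% |

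Entries are power. With no true effect, the rejection rate was 4.6% to 5.6% throughout. So lack of a baseline does not bias the test, heavy loss of power arises only when everything is pooled, and a run-in recovers little of it. The last column is an ideal: it assumes that acute days can be told apart exactly. Splitting respiratory from gut items would not fully achieve that, since a chronic runny nose stays in the respiratory group.

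**The case against.** **The gut symptoms are not lost.** Outcomes {12} compares daily health by arm, so an excess of diarrhoea on the supplement would be recorded and could be seen. Adverse events are collected whatever their relation to the product, and reasons for stopping and new medicines are asked for. This stands, and it limits the point. The symptoms may be missing from the graded adverse-event comparison and may be read as an efficacy outcome, but the trial does hold the data.

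**An article leaves operating rules to the full protocol.** That is fair for how a sheet is transcribed. But {22} states the method of ascertainment and names participants' reports as the source. Which records feed the harms assessment is part of that method.

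**The missing baseline is no error.** Comparing symptoms accrued on treatment between randomised arms is a standard and valid analysis. This stands: long-standing symptoms balance in expectation. In addition, Fig. 2 is not shown and might place the sheet before first intake, although the text of {12} exempts daily health from the baseline measurement. The sentence on positive change may have been meant for the baseline-to-endpoint measures only; if so, it is loose wording.

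**Stronger readings.** A reader might infer that the eight items are merged into one benefit score, so that fewer colds could cancel more gut complaints. The text lists separate items and states no score. A reader might also infer that chronic symptoms will drown the comparison. That needs both pooling and high persistence, and neither is in the documents.

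**Conclusion.** The point holds in a limited form. The stated method of ascertaining adverse events relies on participants' active reports and leaves out a daily record of the most relevant tolerability symptoms. Symptoms ticked by participants who continue can therefore go ungraded. How many is unknown: it depends on symptom rates and on how readily people report, and the documents give neither. The sentence on the expected direction also covers the gut items with no provision for reading them as harm.

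The missing pre-treatment record is a secondary matter of precision. Under the normal approximation with 40 per arm, the detectable difference would fall from 0.63 SD to between 0.60 and 0.45 SD for assumed correlations of 0.3 to 0.7. The true gain depends on how common and how persistent symptoms are. It does not bias the comparison.

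The documents do not support saying that gut intolerance will be hidden, that symptoms are pooled, or that the primary results are affected. Daily health is a supporting outcome. The change is still worth making, because the data already exist and the main step also works for participants already enrolled.

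**What to change.** 1. In {22}, name the daily check sheet as a source of adverse events. Have its entries reviewed, blind to allocation, for new or worsened symptoms, and record these on the case report form with a CTCAE grade whether or not the participant reports them separately.
2. Report days with stomachache, diarrhoea or loss of appetite by arm as tolerability. Report respiratory symptom-days and temperature separately as the immune-related outcome.
3. For participants still to be enrolled, the same sheet could be kept in the week before the baseline visit, when the stool kit is already at home, and used as a covariate. This is optional. If it is not done, state in {12} that the expectation of positive change does not apply to daily health.

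**Cost.** Somewhat more data review and a higher reported adverse-event count, which should be explained in the report as fuller capture. The baseline week adds one week of an existing form. It will be missing for everyone already enrolled (recruitment has run since February 2023), so the adjusted analysis would have a partly missing covariate. Steps 1 and 2 need no new data.
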